This RCT will assess whether PTA within 48 h improves wound healing and reduces complications in participants with chronic ischemic DFUs over a 12-month period compared to standard care. The primary endpoint is the effect of early PTA on wound healing. Secondary endpoints include the combined occurrence of major adverse limb events (MALE), which serve as limb-specific outcomes, and major adverse cardiac events (MACE), which are considered safety-related secondary outcomes. Additional secondary endpoints include time to complete wound healing, major (above-ankle) amputation rate, and the need for new revascularization. Explanatory objectives are changes in wound microbiome composition and local microcirculation. The findings will inform the timing of PTA in managing DFS and help tailor more personalised and effective interventions for T2D persons. The study will also explore whether the baseline wound microbiome can predict healing outcomes.

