## Methods/design

### Study design and randomisation protocol

The PTA-DFS Study is a prospective, monocentric, RCT including participants with T2D and ischemic DFU. Ethics approval was obtained from the local ethics committee (Heinrich Heine University, Düsseldorf, Germany) in accordance with the Declaration of Helsinki (#2022–2291). The PTA-DFS study is registered at www.clinicaltrials.gov (NCT06124586; Registration Date: 2023–08-2).

Participants will be randomly assigned in a 1:1 ratio to either the early PTA group (‘immediate PTA‘ within 48 h after leg artery stenosis (LAS) diagnosis or the elective PTA group (standard of care with PTA within 6 weeks) at the academic hospital of the Heinrich Heine University Düsseldorf, Germany, with inclusion of 200 participants within 5 years. All study participants included in the study will provide informed consent. Although the study is unblinded for both participants and physicians due to practical feasibility, blinding will be applied during the data analysis phase, with separate analysis of primary and secondary endpoints by interventionists (physicians or clinicians) and data analysts to minimise bias. After the data is unblinded, all results will be reviewed collectively. This approach aims to ensure more accurate and unbiased analysis of the primary and secondary endpoints.

Randomisation is performed using a computer-generated sequence with block randomisation to ensure unbiased allocation. The block size will be specified in advance, using blocks of 4 or 6, to maintain balance across groups throughout the study. Both groups receive standard care, with the only difference being the timing of the PTA procedure. The study is structured to ensure that, apart from the timing of PTA, all other aspects of care are consistent across both groups. All subsequent laboratory analyses will be performed in a blinded manner, without knowledge of randomisation. Aside from the timing of PTA, baseline and follow-up examinations will be conducted uniformly across both groups. To optimise recruitment efficiency, training sessions will be held with the interventional angiology staff and the diabetic foot care team, ensuring participants and staff are fully informed about study-related procedures and analyses during their state-of-the-art clinical care.

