### Statistical methods and power calculation

The primary endpoint focuses on the difference in changes of wound area (delta wound area at first - last visit) in T2D participants after early PTA compared to individuals with standard PTA. For the primary—change in wound area after early PTA—and secondary endpoint—combined incidence of MALE and MACE—a power calculation was performed. Assuming a medium effect size (Cohen's d = 0.4), corresponding to 0.4 standard deviations of the difference in delta wound area and difference in time-to-event from baseline to last visit between groups, a sample size of n = 100 per group (total n = 200) is required to achieve 80% power at alpha = 0.05.

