One explanatory variable evaluates the effect of early PTA on wound microbiome dynamics. This objective aims to measure the beta-diversity changes of the wound microbiome, assessed via whole-genome sequencing and analysed using Bray–Curtis distances. In detail, taxonomic profiles from whole-genome sequencing of the wound microbiome will be generated using bioinformatics scripts. The sequencing data, produced via the Oxford Nanopore platform [36] will be analysed with Kraken2 [37] and minimap2 [38] based on a custom database including protozoan, fungal, and viral sequences. Visualisations for comparing metagenomic composition across taxonomic levels will be generated with custom scripts. Principal coordinate analysis based on Bray–Curtis distances will assess sample clustering, with the entire workflow provided as a reproducible Snakemake pipeline [39]. Effect sizes are based on expected changes in Bray–Curtis distances for beta-diversity. Nominal variables will be compared using the Chi-Square Test and Fisher's Exact Test where appropriate. Relationships between variables (e. g., changes in wound microbiome or local microcirculation and wound healing or complications) will be assessed using partial Pearson or Spearman correlation coefficients, with adjustments for confounders and multiple testing via the Bonferroni or Benjamini–Hochberg method. The standardised mean difference (Cohen's d) will be used for power analyses due to the lack of preliminary data on changes of ulcer area and combined incidence of MALE/MACE after early PTA. Changes in beta-diversity of the wound microbiome, will be analysed using Generalised Linear Mixed models with fixed effects including treatment group, bacterial taxa, time, and random effects to account for patient variability. Interaction terms will assess differential effects between treatment groups. The secondary endpoint includes combined MALE and MACE incidence post-angioplasty. Oxygen saturation in wound environment is measured as another explanatory outcome potentially linked to wound healing. Additional outcomes will include an evaluation of risk factors such as comorbidities (severity of anaemia and stages of chronic kidney disease), severity of insulin resistance, DSPN, the duration of hospital stay and interactions with medications, including antibiotics and antithrombotic therapies. Risk endpoints include the incidence of MALE, progression of diabetic complications (e.g., neuropathy), and hospital stay duration. These will be analysed using survival analysis methods and logistic regression to evaluate risk/benefit ratios. Multiplicity will be addressed as follows: The primary outcome will be analysed at a two-sided significance level of 0.05 without adjustment. For the prespecified family of confirmatory secondary outcomes, the family-wise error rate will be controlled at 0.05 using the Holm–Bonferroni procedure. For these outcomes, raw and adjusted p-values as well as corresponding adjusted 95% confidence intervals will be reported. Exploratory outcomes will not be adjusted for multiplicity and will be clearly identified as exploratory. Safety outcomes will be reported descriptively. The interaction effects of antibiotics, PTA timing, and concomitant antithrombotic treatments on both primary and secondary endpoints will be assessed using logistic regression models and subgroup analyses. Time-to-event clinical endpoints will be analysed with Kaplan–Meier survival curves, while covariate adjustments will be incorporated using Cox proportional hazards models. Correlation analyses (partial Pearson or Spearman coefficients) will account for confounders and include multiple comparison corrections via Bonferroni or Benjamini–Hochberg adjustments. Categorical variables will be compared using Chi-Square or Fisher's Exact Tests, while continuous variables will be analysed with Wilcoxon rank-sum tests or Student's t-tests, as appropriate. Two-tailed p-values below 0.05 will be considered statistically significant. Missing data will be summarised by variable, time point, and treatment arm, and patterns of missingness will be described graphically and statistically. The primary analysis will employ multiple imputation by chained equations (MICE; m = 20 imputations) under the assumption of missing at random (MAR). The imputation model will be specified to be congenial with the planned analysis and will include treatment arm, relevant baseline covariates (e. g., age, sex, ulcer duration, ulcer size, Wagner grade, HbA1c, infection status), and outcome variables. Continuous variables will be imputed using predictive mean matching, binary variables will be analysed via logistic regression, and ordinal variables will be analysed using proportional-odds models. Estimates will be combined using Rubin’s rules. Sensitivity analyses will include (i) complete-case analysis, (ii) best–worst and worst–best case scenarios, and (iii) a delta-adjusted pattern-mixture model to assess departures from MAR and exploring missing not at random (MNAR). All statistical analyses will be performed using the R Version 4.4 and SPSS for Windows 23.0 (SPSS Inc., Chicago, IL, USA). Figures are created with GraphPad Prism, Version 7.01 (GraphPad Software, Inc., La Jolla, CA, USA) or R, and Graphical abstracts using BioRender.com.

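### The primary analysis imputes wound area under MAR with no exception for death or major amputation, and Kaplan–Meier for time to healing would overstate healing

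*Protocol article*

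**What the plan says.** All of the following is in the Protocol article. Unless another section is named, it is in Statistical methods and power calculation.

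- The primary endpoint is the change in wound area, given as "delta wound area at first - last visit". It is tested two-sided: "The primary outcome will be analysed at a two-sided significance level of 0.05 without adjustment".
- On missing data: "The primary analysis will employ multiple imputation by chained equations", with 20 imputations, under missing at random (MAR). Continuous variables use predictive mean matching. The model holds treatment arm, baseline covariates and outcome variables; which outcome variables is not said.
- The sensitivity analyses are complete case, best–worst and worst–best scenarios, and a delta-adjusted pattern-mixture model.
- For event outcomes: "Time-to-event clinical endpoints will be analysed with Kaplan–Meier survival curves", with Cox models for covariate adjustment. No censoring rule and no competing-risk method are given.
- Background: "Additional secondary endpoints include time to complete wound healing, major (above-ankle) amputation rate, and the need for new revascularization". The Outcome monitoring section adds that amputations and deaths from any cause are followed for 12 months.
- Imaging and ulcer evaluation: wound documentation ends once closure has been confirmed.

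The article does not separate a wound area that was not measured from one that cannot exist.

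**The concern.** After death or above-ankle amputation of the index limb there is no wound to measure, so its area is undefined rather than missing. MAR imputation answers the question of what area would have been recorded had someone looked, which has no meaning for these participants. Predictive mean matching draws only values that were actually observed, so every donor is a participant with a measurable wound and no failure value can be imputed.

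The trial asks whether earlier PTA helps participants at risk of limb loss. If the arms differ in deaths or amputations, the primary result takes in that difference weakly or not at all, and the arm with more failures gains. This could hide a benefit or a harm.

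Two related gaps matter. Because documentation stops at closure, healed participants also lack later areas unless a rule sets them to zero. And for time to complete healing, a Kaplan–Meier curve that censors dead or amputated participants treats them as still able to heal.

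**Working it through.** **1. The plan's own figure.** Inputs: d = 0.4, 80% power, two-sided 0.05, 1:1 allocation. n per arm = 2 × (1.960 + 0.842)² / 0.4² = 98.1, so 99; the t-test version gives 99.08, so 100. Power at 100 per arm is 0.80 to 0.81. This agrees with "a sample size of n = 100 per group (total n = 200) is required to achieve 80% power at alpha = 0.05". The figure has no allowance for dropout or for failures.

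**2. Event rates (assumption).** The article gives no rates for this trial. Its Background cites limb preservation of up to 94% (about 6% limb loss) and amputation at any level in about 20% of foot infections. I use 6% to 20% per arm as a bracket for death or major amputation.

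**3. What MAR imputation does.** Simulation with 200,000 per arm and true difference 0.40 SD. Failures occur mainly in poor healers, and within-arm regression imputation from one interim wound area stands in for predictive mean matching. The latent value is a notional area reduction, in SD.

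| Control-arm failures | Latent mean, failures | Imputed mean, failures | Mean, survivors |
|---|---|---|---|
| 10% | −1.46 | −0.35 | 0.16 |
| 20% | −1.17 | −0.12 | 0.29 |

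Imputed values lie much nearer to the survivors than to the latent values, but are not equal to the survivors.

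| Failures, elective / early | Estimated difference (latent 0.40) |
|---|---|
| 10% / 10% | 0.40 |
| 20% / 20% | 0.40 |
| 20% / 10% | 0.30 |
| 10% / 20% | 0.49 |

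With equal rates the estimate barely moves. With unequal rates it moves towards the arm with more failures.

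**4. Scoring failures as failures.**

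As zero reduction: assume survivors' mean reduction is 1 SD in the elective arm and 1.4 SD in the early arm. The difference is (1 − q_early) × 1.4 − (1 − q_elective) × 1.
- 10% in both: 0.9 × 1.4 − 0.9 = 0.36
- 20% elective, 10% early: 0.9 × 1.4 − 0.8 = 0.46
- 10% elective, 20% early: 0.8 × 1.4 − 0.9 = 0.22

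As worst rank: d = 0.4 in survivors, 10% failures in both arms.
- P(early better) = 0.9 × 0.1 + ½ × 0.1² + 0.9² × Φ(0.4/√2) = 0.090 + 0.005 + 0.81 × 0.611 = 0.590
- Null SE = √(201 / (12 × 100 × 100)) = 0.0409
- z = 0.090 / 0.0409 = 2.20; power = Φ(2.20 − 1.96), about 60%

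**5. Time to healing (assumed hazards).** Healing hazard h = 1.0 per year; hazard of death or major amputation c = 0.15 to 0.25 per year.
- 1 − Kaplan–Meier with censoring: 1 − e^(−1) = 63.2%
- True cumulative incidence: h/(h + c) × (1 − e^(−(h + c)))
- c = 0.15: (1/1.15) × (1 − 0.317) = 59.4%
- c = 0.25: (1/1.25) × (1 − 0.287) = 57.1%

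The overstatement is 3.8 to 6.1 percentage points.

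**6. Whether the sensitivity analyses repair it.** Best–worst and worst–best scenarios assign opposite values to the two arms, so each scores one arm's failures as successes. The delta adjustment, as described, does not separate deaths and amputations from missed visits. None scores these events as failure in both arms, and none changes the primary result.

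**The case against.** The case on the other side has several good parts.

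- **The plan does not say that these areas are imputed.** That follows only from the absence of an exception, and an analysis plan that is not shown may supply one. This stands as a caution. Still, the article fixes the imputation method, covariates, pooling and sensitivity analyses, so the rule as published is the one to correct.
- **Last visit may mean last attended visit.** Most such participants would then have an observed area and little would be imputed. This stands, and is a reason to define the term. The later death or amputation would still not count in the primary result.
- **The model includes outcome variables.** Earlier areas can carry information, and the simulation shows that they do. A reader might infer that failures simply receive the healing of intact survivors; that is only the limiting case.
- **Limb loss is not ignored.** Major amputation and the MALE/MACE composite are secondary endpoints, and wound-area change is a legitimate primary question. This stands: whether these events belong in the primary estimand is a choice, but it must be stated.
- **Censoring is not in the text.** A reader might infer that the protocol censors death and amputation, or scores an amputated limb as area zero. It says neither. Censoring is the usual practice with Kaplan–Meier when no other rule is given. The point does not carry over to MALE/MACE, whose components are not defined and may include these events.
- **Cox already gives a cause-specific hazard ratio when competing events are censored.** This is correct. Only the curve is biased.

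**Conclusion.** The concern holds in limited form. The published rule makes no exception for wound areas that cannot exist, and followed literally it favours the arm with more deaths and major amputations. The illustrative shift is about 0.1 SD either way when failures are 10% in one arm and 20% in the other, and close to nil when rates are equal. These figures rest on assumed rates, on failures occurring mainly in poor healers, and on a regression stand-in for predictive mean matching.

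A reader might infer that the plan works against early PTA. The documents do not support a direction, because they give no event rates by arm. The stated sample size reproduces and is not affected by the imputation rule.

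For time to healing, the overstatement of about 4 to 6 points depends on the assumed hazards and on the usual censoring.

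The documents do not compel a worst-rank composite as the primary endpoint. That would redefine the endpoint and, with 10% failures in both arms, lower power at d = 0.4 from about 80% to about 60%.

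**What to change.** 1. **Imputation.** Restrict multiple imputation to visits missed by living participants with the index limb intact. Set area to zero after confirmed closure. Define the last visit: the scheduled 12-month visit or the last one attended.
2. **Estimand.** State how death and major amputation of the index limb enter the primary estimand. Prespecify at least one supplementary analysis that scores them as failure in both arms, for example a worst-rank Wilcoxon test. If this is made primary, restate the power.
3. **Time to event.** For time to healing, report Aalen–Johansen cumulative incidence in place of 1 − Kaplan–Meier, with death and major amputation as competing events. Do the same for amputation and revascularisation, with death as the competing event. Label Cox results as cause-specific hazard ratios.

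Cost: items 1 and 3 and a supplementary analysis need only wording and a little more analysis work, since these events are already monitored. Reported healing proportions will be slightly lower. Making the failure-scored analysis primary costs more: a protocol amendment, a new power calculation, and an effect measure that is no longer a mean area difference.

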
## Discussion

This study investigates the effect of an early revascularisation timing on changes in wound area as well as clinical outcomes in individuals with chronic-ischemic DFU in T2D. Conducted among consecutively enrolled and prospectively followed participants treated by a multidisciplinary foot team, this is the first RCT to examine the impact of revascularisation timing on wound healing and potentially healing-associated explanatory factors such as wound microbial dynamics and changes in local microcirculation in individuals with PAD and DFU in T2D.

### Recommendations for Timing of Endovascular Therapy in Chronic-Ischemic DFU

The selected time frame for early treatment (within 48 h) was conceptually adapted from the ESC guidelines on non–ST-elevation acute coronary syndrome (NSTE-ACS), which recommend an early invasive approach within 24–72 h to prevent ischemic progression and improve outcomes. While the pathophysiology of coronary artery disease and PAD differs, the underlying principle—namely, that timely reperfusion limits tissue damage—can be applied to the context of critical limb ischemia in patients with DFS. This is supported by an observational study, which indicated that a shorter time to revascularisation (within 8 weeks) is correlated with a higher likelihood of healing in ischemic foot ulcers and limb salvage rates [40]. The time frame for follow-up visits with every 4 week examinations over 3 month is based on a post-hoc analysis suggesting that a four-week evaluation period assessing the percent change in DFU area is a robust predictor of healing at 12 weeks [41].

Limited information exists regarding the prospective outcomes of revascularisation in T2D persons with PAD and DFU. One study showed that persons with PAD who underwent revascularisation were nearly 15 times more likely to achieve wound healing compared to those who did not, with ulcer severity influencing the healing outcome [42]. Delays in revascularisation may exacerbate hypoxic conditions, favouring anaerobic bacterial proliferation, inflammation and impairing wound healing. In addition, the 48-h window represents a clinically feasible and operationally meaningful target in modern multidisciplinary diabetic foot care. Thus, this threshold balances pathophysiological urgency with realistic logistics in specialised vascular settings.

### Effects of endovascular treatment on microcirculation and wound healing

An RCT involving participants with critical limb ischemia found that poor baseline microcirculatory skin perfusion was linked to high amputation rates after 18 months [43]. Previous studies have shown that PTA not only improves macrocirculation but also positively impacts microcirculation. Changes in wound tissue oxygen saturation measured by NIRS correlated with wound area reduction, unlike ABI, which may be unreliable in persons with diabetes with media sclerosis [34]. As a non-invasive method for measuring tissue oxygenation and blood flow in the local wound environment, NIRS analyses could serve as a complementary tool to standard clinical assessments (e.g., ABI, toe-brachial index, Doppler ultrasound, transcutaneous oxygen pressure, and angiography) for evaluating microcirculatory changes after early PTA, warranting further investigation in DFU treatment strategies.

### Impact of the wound microbiome on DFU healing

Increased presence of *Lactobacillus* species has been associated with enhanced wound healing [44]. The microbiome in DFU is also different from that of unaffected skin in persons with diabetes, with skin in these individuals showing less microbial diversity compared to those without diabetes [45]. Breaches in the skin barrier expose tissue to microbial contamination, leading to infection, delayed healing, and further tissue damage. Certain strains of *Staphylococcus aureus*, *Pseudomonas aeruginosa*, *Enterococcus* spp. and *Escherichia coli* have been linked to chronic wound infections [46–48]. Pathogens that commonly infect wounds, such as *Staphylococcus aureus* and *Pseudomonas aeruginosa* express virulence factors and form biofilms, evading immunity and resisting therapies, which complicates healing [49]. Biofilm-related genes are more abundant in non-healing DFUs, highlighting the importance of microbial functional capabilities such as biofilm production in chronic wound management [45].

### Temporal dynamics of the wound microbiome

Studies indicate that rapid changes in microbial populations correlate with faster healing and better outcomes in DFU [45, 50]. Shotgun metagenomics studies show strain-specific variations, with some strains of *Staphylococcus aureus* linked to non-healing wounds, while others, like *Alcaligenes faecalis*, may not impede healing [50]. For instance, synergistic interactions between *S. aureus* and *P. aeruginosa* may exacerbate wound infections, while certain commensals may inhibit pathogen growth [45]. Understanding these microbial dynamics opens avenues for targeted therapies, including probiotics and microbiome modulation, to promote healing in DFU.

